## Abstract

**Background:**

Child maltreatment, a major public health concern, has long-term neurobiological, psychological, and social consequences. Recognizing, documenting, and reporting suspected cases should be systematic across hospital and community services, but these processes are hindered by inconsistent surveillance systems, uneven professional training, and the lack of standardized data collection tools. Timely follow-up, updated clinical criteria, and structured multidisciplinary training can improve case assessment, traceability, and professionals’ ability to report suspected maltreatment. The Sentinel project was developed to address these clinical, organizational, and public health gaps through a combined REDCap-based digital registry and structured training program for pediatric health care professionals.

**Objective:**

This study aims to evaluate the usability, feasibility, and preliminary impact of an integrated surveillance and training system designed to improve the early detection, documentation, and reporting of suspected child maltreatment by pediatricians and health care professionals.

**Methods:**

This is an observational, exploratory, monocentric pilot implementation study with a pretest-posttest evaluation design. The study will be conducted over 24 months in a hospital-community pediatric network. Voluntary participants will be hospital and community pediatricians and other pediatric health care professionals who provide written informed consent. The project includes two interconnected components: (1) implementation of a secure, anonymized REDCap registry for standardized documentation of suspected maltreatment, follow-up, reporting pathways, and case management outcomes and (2) a theoretical-practical training program delivered through lectures, e-learning modules, webinars, supervised exercises, and hands-on registry sessions. Primary and secondary outcomes will be assessed at prespecified time points, including baseline, immediately after training, during registry use, and at the end of follow-up. Registry usability will be measured using the System Usability Scale; training effectiveness will be measured through pretest-posttest knowledge, competency tests, and satisfaction questionnaires; and reporting outcomes will be measured through comparison of pre- and postimplementation reporting rates.

**Results:**

The study will report the usability, feasibility, and preliminary implementation outcomes of the integrated registry training system. Main results will include System Usability Scale scores, registry completion indicators, reporting timeliness, the number and rate of suspected maltreatment reports before and after implementation, changes in knowledge and competency scores, participant satisfaction, and qualitative feedback on barriers to and facilitators of implementation. Participant recruitment and data collection began in April 2026 and are currently ongoing. Completion of data collection and publication of the results are expected between December 2027 and January 2028.

**Conclusions:**

The Sentinel project will test an innovative and scalable pilot model that integrates digital surveillance with structured professional training to enhance the early detection, documentation, and management of suspected child maltreatment. By standardizing data collection, strengthening professional competencies, and fostering collaboration across hospital and community settings, the study will inform the development of a regional or national observatory and support an evidence-based, system-wide approach to child protection.

**Trial Registration:**

ClinicalTrials.gov NCT07250074; https://clinicaltrials.gov/study/NCT07250074

**International Registered Report Identifier (IRRID):**

PRR1-10.2196/89128

## Introduction

### Theoretical Context and Framing of the Problem

Child maltreatment and abuse represent one of the most serious and persistent public health and social emergencies of the 21st century, with profound repercussions on neurobiological development, emotional regulation, mental health, physical health, social functioning, and life-course well-being [1-14]. These consequences make early identification and timely protection a core responsibility of pediatric and public health systems rather than a problem confined to social or judicial services.

The World Health Organization defines child maltreatment as any form of physical, sexual, or psychological abuse, neglect, or exploitation that results in actual or potential harm to the child’s health, survival, or dignity [1,12]. According to the *Global status report on preventing violence against children 2020* [13], approximately 1 billion children worldwide experience some form of violence each year. The consequences of such experiences often persist into adulthood, increasing the risk of psychiatric disorders, chronic diseases, and relational dysfunctions [2-6].

Available national and institutional data show that child maltreatment remains difficult to quantify, with recorded cases representing only the visible part of a largely underestimated phenomenon [15-18]. Underrecognition, delayed reporting, heterogeneous procedures, and limited surveillance systems hinder health services’ ability to monitor suspected cases, describe their epidemiology, and evaluate the timeliness and effectiveness of protective responses [15-18].

Scientific literature demonstrates that early exposure to violence or neglect induces lasting alterations in neuroendocrine circuits and in the regulation of stress responses [19-24]. Witnessed violence, in which a child is exposed to aggressive acts within the family environment, produces psychological effects comparable to those observed in direct survivors [25-27]. These findings emphasize the urgent need for early, integrated, and data-driven interventions aimed at prevention, identification, and timely protection.

### State of the Art and Operational Gaps

Despite significant legislative advances and an increasing cultural awareness of child protection, the management of child maltreatment in Italy remains heterogeneous and fragmented [17]. Reporting procedures vary widely across regions and services, and the absence of a unified information system hampers both the epidemiological analysis of cases and the assessment of intervention effectiveness.

Health care professionals, particularly pediatricians, occupy a pivotal position in the early identification of abuse and neglect because they may observe sentinel injuries, developmental concerns, psychosomatic symptoms, family risk factors, or repeated access to care before other agencies become involved [28-31]. Nevertheless, recognition and reporting require not only clinical awareness but also shared definitions, standardized documentation, clear legal-operational pathways, and confidence in interprofessional communication. The absence of these supports contributes to underreporting; delayed notification; incomplete documentation; and inconsistent coordination among hospitals, community pediatrics, social services, and child protection authorities [17,19,28-32].

At the international level, clinical registries have been used to improve data quality, case traceability, auditability, and the monitoring of care pathways, particularly when data items are standardized and embedded in routine clinical workflows [33-36]. In parallel, structured and multidisciplinary educational programs have been associated with improvements in knowledge, recognition skills, confidence, and reporting behavior among health care professionals involved in child protection [37-43]. These findings support an integrated model in which digital infrastructure and professional education are implemented together rather than as isolated quality improvement activities.

Nevertheless, in Italy, there is still no established model that systematically combines technological innovation, professional training, and territorial governance in addressing child maltreatment. The Sentinel project seeks to fill this critical gap by integrating these dimensions into a unified and evidence-based framework capable of supporting both clinical practice and policy development.

### Hypothesis and Rationale of the Project

In light of these critical issues, the Sentinel project was conceived to create an integrated surveillance and training system for the early recognition of suspected child maltreatment, combining technological innovation, professional education, and hospital-community coordination.

The underlying hypothesis is that the combination of a standardized digital registry and a structured training program for pediatricians and health care professionals can significantly improve the capacity of the health care system to identify, document, and respond to cases of suspected maltreatment. Specifically, the project assumes that this integrated approach will (1) enhance the early detection of suspected child abuse and neglect; (2) improve the quality, completeness, and timeliness of reporting; and (3) strengthen collaboration between hospital and community-based services, thereby increasing the efficiency of multidisciplinary care for vulnerable children.

The registry, developed using the REDCap platform (Vanderbilt University), will enable the anonymous and standardized collection of clinical and social data while ensuring data security, traceability, and compliance with privacy regulations.

In parallel, the training component, structured through theoretical and practical modules, will provide health care professionals with the clinical, communication, legal, and operational skills required to recognize warning signs, activate reporting pathways, document case information, and use the registry appropriately. This dual approach is designed to promote a shared language and a consistent, evidence-based methodology among pediatric and allied health professionals.

### Scientific Significance and Expected Impact

The Sentinel project adopts a translational research perspective, aiming to transform scientific evidence into operational tools and effective prevention policies. By integrating data collection with continuous professional training, the project bridges the gap between research and clinical practice, promoting the direct application of evidence to improve child protection.

Sentinel aspires to validate a replicable model of clinical-epidemiological surveillance of child maltreatment capable of generating robust data for health planning and fostering a cultural shift within community pediatrics toward proactive identification and intervention. The integration of technology and education establishes an innovative paradigm in which digital systems support professional empowerment and, ultimately, the protection of children at risk.

In the long term, this initiative aims to lay the groundwork for the establishment of a regional observatory on child maltreatment with the potential for national expansion. Such an observatory would provide a sustainable infrastructure for continuous surveillance, professional education, and policy development, ensuring that child protection becomes a structural and data-informed component of public health systems.

### Aim of the Study

The aim of this study is to evaluate the usability, feasibility, and preliminary implementation impact of the Sentinel digital registry and training network in improving standardized case identification, documentation quality, reporting timeliness, and case management among hospital and community pediatric health care professionals.

## Methods

### Study Design

The Sentinel study is an observational, exploratory, monocentric pilot implementation study with a pretest-posttest evaluation design and an overall duration of 24 months. The project does not introduce an experimental clinical treatment and does not modify the legal or clinical duties of professionals involved in suspected child maltreatment. Rather, it evaluates the implementation of 2 organizational tools: a secure digital registry for standardized documentation and a structured training program for pediatric health care professionals. The primary objective is to assess registry usability and feasibility. Secondary objectives are to evaluate training effectiveness, reporting completeness, reporting timeliness, and preliminary changes in suspected maltreatment reporting rates before and after implementation.

The project is organized into 2 interconnected components: the registry component and the training component. These components will be implemented sequentially and then evaluated jointly because the registry is intended to standardize documentation, whereas training is intended to improve recognition, case management confidence, and appropriate use of the registry.

The operational sequence will include development and internal testing of the REDCap registry; definition of the minimum dataset and reporting workflow; recruitment of hospital and community pediatric professionals; baseline assessment of knowledge, competencies, and reporting activity; delivery of the training program; activation of registry data entry; continuous monitoring of registry completeness and technical issues; follow-up assessment of outcomes; statistical analysis; and dissemination of results. All activities will be coordinated by an internal scientific committee responsible for methodological quality, ethical compliance, data protection procedures, and adherence to project timelines.

Because of its observational and pilot implementation nature, the study will not interfere with clinical decision-making, child protection duties, or mandatory reporting obligations. Professionals will continue to follow existing institutional and legal procedures for suspected maltreatment. Study data will be used only to evaluate registry use, reporting activity, and educational outcomes and identify preliminary indicators of feasibility, usability, acceptability, and implementation impact that can inform future multicenter or regional surveillance models.

### Study Setting and Timeline

The study will be conducted within the coordinating pediatric hospital and its connected community pediatric network. The 24-month timeline will include approximately 3 months for registry development and internal testing, 3 months for recruitment and baseline assessment, 3 months for training delivery, 12 months for registry activation and follow-up data collection, and 3 months for final analysis and dissemination. Minor adaptations to these periods may be made according to ethics approval timelines and operational feasibility.

### Participants and Recruitment

The study population will consist of health care professionals from the regional pediatric network, including hospital and community pediatricians, pediatric residents, nurses, psychologists, and other professionals involved in the recognition, documentation, or management of suspected child maltreatment according to local organizational arrangements.

Recruitment will occur through institutional invitations circulated within the hospital-community pediatric network. Participation will be voluntary and require written informed consent. Eligible participants will be professionals aged 18 years or older who work in pediatric or child health settings, attend the training program, and agree to complete the evaluation questionnaires. Participants will be asked to complete baseline and posttraining assessments and, where applicable, use the registry during the implementation period.

Exclusion criteria will comprise refusal or withdrawal of consent, failure to complete the training program, nonparticipation in the practical registry sessions, or missing primary outcome data for the relevant analysis. A minimum of 30 professionals will be targeted. This sample is considered appropriate for a pilot feasibility study and for preliminary estimation of usability, training gains, and reporting process indicators.

### Implementation Components and Procedures

#### Registry Component

The digital registry will be developed using the REDCap platform, a system widely used in clinical research for secure data collection, management, and analysis. The registry will be configured with role-based access, audit trails, structured data entry fields, mandatory and optional variables, and data quality checks. Access will be restricted to authorized project personnel, and all data management procedures will comply with applicable institutional policies and data protection regulations.

The registry will collect only anonymized or non–directly identifiable information required for research and service evaluation. Data fields will include child age group and sex, date and setting of contact, type of suspected maltreatment (physical, psychological, or sexual maltreatment; neglect; or exposure to domestic violence), warning signs, risk and protective factors, reporting source, referral or follow-up arrangements, and case management outcome. Each record will be assigned a unique alphanumeric study code. Direct identifiers, such as name, fiscal code, address, telephone number, or full date of birth, will not be entered into the research registry. Potential duplicate reports will be managed through predefined nonidentifying linkage variables, including time window, age group, sex, setting, and event characteristics, without attempting to reidentify the child.

Registry usability will be evaluated using the System Usability Scale (SUS), a validated 10-item questionnaire yielding scores from 0 to 100 [44]. SUS completion will be restricted to trained and authorized professionals with documented exposure to the registry, as detailed in the Outcomes and Measurement Time Points section. Feasibility indicators will include number of active users, number of records created, proportion of completed mandatory fields, average time required to complete a report, number of technical support requests, proportion of records with documented pathway activation, and completeness of follow-up fields. These indicators will allow for evaluation of whether the registry reduces data fragmentation and supports standardized clinical and operational terminology.

The impact of the integrated registry training system on suspected maltreatment reporting will be assessed by comparing pre- and postimplementation reporting rates. The numerator will be the number of suspected maltreatment reports recorded during each observation period. The denominator will be the number of participating professionals and, when available, the number of pediatric consultations or service contacts during the same period. Reporting rates will therefore be expressed as reports per professional month and, where denominators are available, reports per 1000 pediatric contacts.

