### Outcomes and Measurement Time Points

The primary outcome is registry usability, measured using the mean SUS score collected after participants use the registry. Specifically, the SUS will be administered once at the end of the 12-month registry activation and follow-up period or earlier for participants who discontinue participation after having completed the minimum required registry exposure. Eligible respondents will be trained and authorized hospital or community professionals involved in suspected maltreatment recognition, documentation, or case management. To ensure that SUS responses reflect actual exposure to the tool, participants will be included in the primary SUS analysis only if they have entered at least one registry record or completed at least one supervised registry use session or simulation. Participants without any registry exposure will not contribute to the primary SUS analysis.

Secondary outcomes include feasibility indicators (active users, number of records, completion of mandatory fields, technical support requests, and time to complete a report), training outcomes (pretest-posttest knowledge and competency scores, satisfaction, and qualitative feedback), and reporting outcomes (number and rate of suspected maltreatment reports, reporting timeliness, duplicate reports, follow-up documentation, and activation of child protection pathways). Baseline data will be collected before training and registry activation, posttraining outcomes will be collected immediately after training, and registry usability and implementation outcomes will be collected during registry use and at the end of the observation period.

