### Data Management, Confidentiality, and Registry Workflow

Registry data will be entered using predefined forms by trained and authorized professionals. Records will be entered by the professional who identifies or manages the suspected case or by another authorized member of the clinical team directly involved in the case according to local organizational arrangements. Follow-up information will be updated when new nonidentifying information becomes available regarding referral, pathway activation, multidisciplinary evaluation, or case management outcome. Records will be saved under a unique study code and stored on secure institutional servers or approved REDCap infrastructure. The registry will not contain direct identifiers. Data access will be role based and limited to authorized members of the research team. Data exports for analysis will be anonymized, stored in password-protected files, and used only for the objectives approved by the ethics committee. Data quality will be checked periodically by designated members of the research team through REDCap validation rules, completeness checks, audit trails, and review of mandatory fields. Any inconsistencies, missing mandatory information, or potential duplicate records will be resolved using only nonidentifying registry information. Potential duplicate reports will be assessed through predefined nonidentifying linkage variables, including time window, age group, sex, setting, and event characteristics. When a potential duplicate is detected, the research team will retain a single registry record for analysis and update it with additional nonidentifying information when appropriate. Duplicate management will not involve access to direct identifiers and will not interfere with clinical or legal reporting procedures.

Any suspected maltreatment identified in clinical practice will continue to be managed through ordinary institutional and legal reporting pathways; the registry is an evaluation and documentation tool and does not replace mandatory reporting procedures. Mandatory reporting will remain a separate clinical and legal process carried out through existing institutional channels and according to applicable law. Entry of information into the research registry will be separate from the activation of the appropriate clinical and legal pathway and will not be considered a substitute for mandatory reporting. No direct identifiers or legal reporting documents will be uploaded to the registry.

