### Statistical Analysis

#### Overview

Quantitative analyses will be performed using recognized statistical software, such as SPSS, R, or Stata. Descriptive statistics will be calculated for all study variables. Continuous variables will be summarized as means and SDs or medians and IQRs according to distribution. Categorical variables will be summarized as frequencies and percentages. All estimates will be reported with 95% CIs when appropriate.

Pretest-posttest comparisons of knowledge and competency scores will be performed using 2-tailed paired-sample *t* tests when normality assumptions are met, as assessed using the Shapiro-Wilk test and visual inspection of distributions. When assumptions are not met, Wilcoxon signed-rank tests will be used. Mean change scores, standardized effect sizes, and 95% CIs will be reported to support interpretation of training effectiveness.

Registry usability will be evaluated by calculating the mean SUS score and comparing it with established interpretive benchmarks, where scores of 70 or higher are considered acceptable and scores of 80 or higher indicate excellent usability [44]. A 1-sample *t* test or Wilcoxon signed-rank test will be used to compare observed SUS scores with the prespecified benchmark depending on distributional characteristics.

Changes in reporting rates of suspected child maltreatment before and after implementation will be analyzed using Poisson regression models, estimating incidence rate ratios with 95% CIs. The primary pretest-posttest comparison will use reports per professional month as the operational denominator. When service volume data are available, additional models will use the number of pediatric consultations or contacts as an offset to estimate reports per 1000 contacts. Overdispersion will be assessed by comparing the deviance and Pearson chi-square statistics with the df; if overdispersion is present, negative binomial regression or robust SEs will be applied. Repeated reports and potential duplicates will be described separately and, in sensitivity analyses, excluded or counted once per suspected case according to the predefined duplicate management rules.

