### Registry Phase Results

The registry component will generate implementation results on the use of the REDCap platform for systematic, secure, and standardized recording of suspected child maltreatment reports [45]. Reported results will include the number of trained users, number of active registry users, number of records created, completion of mandatory fields, time required for report completion, and number of technical or workflow issues identified during implementation.

The analysis will describe whether the registry provides a more unified view of suspected cases and care pathways than the preimplementation documentation process. Completeness, traceability, documented actions, follow-up fields, and pathway activation will be used as operational indicators of report quality.

Registry usability will be described using SUS scores, reported as means, SDs, medians, IQRs, 95% CIs, and the proportion of scores below 70 and above 80 [44]. To evaluate implementation, reporting rates will be compared before and after registry introduction and expressed as reports per professional month and, where denominators are available, per 1000 pediatric contacts.

The registry will describe suspected cases by maltreatment type, child characteristics, family and social context, access route, setting, referral pathway, follow-up, and outcome. These data will help assess whether the model can generate useful local information to support prevention strategies, service indicators, and health care planning.

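### The pre-post reporting rate counts reports as recorded, but the registry exists only in the post period, so the incidence rate ratio can move with no change in reporting

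*Protocol article*

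**What the plan says.** Registry Component defines the outcome: "The numerator will be the number of suspected maltreatment reports recorded during each observation period". It names no data source for either period. Statistical Analysis (Overview) sets the denominator, "The primary pretest-posttest comparison will use reports per professional month as the operational denominator", and the model: changes in rates "will be analyzed using Poisson regression models, estimating incidence rate ratios with 95% CIs". Contacts serve as an offset where service volume is known. Overdispersion is checked, and repeat or duplicate reports are handled in sensitivity analyses under predefined duplicate rules.

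Registry Phase Results presents the registry as the platform for recording suspected maltreatment reports and states that "reporting rates will be compared before and after registry introduction".

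On timing, Outcomes and Measurement Time Points says "Baseline data will be collected before training and registry activation". Study Design lists a "baseline assessment of knowledge, competencies, and reporting activity" without giving its source or look-back period. Study Setting and Timeline allots about "3 months for recruitment and baseline assessment", 3 months for training and 12 months for registry activation and follow-up.

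Data Management, Confidentiality, and Registry Workflow keeps mandatory reporting in its existing channels and adds: "Entry of information into the research registry will be separate from the activation of the appropriate clinical and legal pathway".

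**The concern.** The event that divides the two periods is the arrival of the recording tool. Before it, reports can be counted only from whatever documentation already existed. After it, there is a structured form with mandatory fields, trained users and periodic completeness checks. If post-period counts come from the registry and pre-period counts from elsewhere, the IRR compares two ascertainment systems as well as two levels of reporting behaviour, and the analysis cannot separate them.

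This matters because the reporting rate is the only reporting outcome given a pre-post model, and Registry Component presents it as the assessment of the system's impact on reporting. The Discussion also expects to show how gains in competence influence reporting behaviour. A rise produced by better recording would be read as that effect. The Limitations section mentions registry data quality but not a difference in ascertainment between the periods.

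**Working it through.** The article gives no baseline rate, expected IRR or event count for this comparison, so there is no stated figure to reproduce. The check has three steps.

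**1. What each period can count.** Baseline precedes activation, so pre-period counts cannot be prospective registry records. For the post period, three parts of the text point to the registry. Registry Phase Results describes it as the means of recording reports. Registry Component lists the time to complete a report among the registry's feasibility indicators. The duplicate rules that the rate analysis relies on (Registry Component; Data Management) work by keeping a single registry record. Since a registry entry is separate from activating the formal pathway, a registry record and a formal report are different events.

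**2. Expected IRR with no change in reporting.** Let λ be the true rate, constant over time, and c0 and c1 the fractions captured before and after.

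IRR = (λ × c1) / (λ × c0) = c1 / c0

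The capture fractions are assumptions.

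| c0 | IRR if c1 = 1.0 | IRR if c1 = 0.9 |
|---|---|---|
| 0.9 | 1.11 | 1.00 |
| 0.8 | 1.25 | 1.12 |
| 0.7 | 1.43 | 1.29 |
| 0.6 | 1.67 | 1.50 |
| 0.5 | 2.00 | 1.80 |

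The ratio can also fall below 1. If formal logs caught every case before and the registry caught 80% after, the IRR would be 0.8 / 1.0 = 0.80.

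Capture acts on the numerator, so using professional-months or contacts as the offset leaves c1/c0 unchanged. Negative binomial regression or robust standard errors change the interval, not this ratio. Removing duplicates does not put the two periods on a common source.

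**3. Chance of P<.05 with no true change.** Inputs from the article are 30 professionals (the minimum target), a 12-month post period and a two-sided 5% level. The assumptions are a rate of 0.2 reports per professional-month, c1 = 1.0, Poisson counts, and a pre-period of 3 or 12 months, because its length is not stated. The formulas are μ = λ × c × 30 × months, SE(log IRR) = √(1/μ0 + 1/μ1), and a Wald test.

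For c0 = 0.6:
- 3-month pre-period: μ0 = 0.2 × 0.6 × 30 × 3 = 10.8 and μ1 = 0.2 × 30 × 12 = 72. SE = √(1/10.8 + 1/72) = 0.326, and log(1.667)/SE = 0.511/0.326 = 1.57. The chance of significance is 35%.
- 12-month pre-period: μ0 = 43.2, SE = 0.192 and the ratio is 2.65. The chance is 76%.

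At the same rate, c0 = 0.8 gives 12% (3 months) and 24% (12 months), and c0 = 0.5 gives 50% and 92%. With c0 = 0.6 and assumed rates from 0.05 to 0.5, the chance runs from 12% to 70% (3 months) and from 26% to 99% (12 months). With equal capture (c0 = c1), the expected IRR is 1.00 and the chance is the nominal 5%. A longer baseline therefore does not cure the problem: it makes a biased ratio more likely to reach significance.

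**The case against.** The strongest reply is that nowhere does the article say that the post-period numerator consists of registry records. Outcomes and Measurement Time Points lists the number of records under feasibility, separately from the number and rate of suspected maltreatment reports. Institutional reporting continues throughout, so a common source is possible under the text, and naming it could be left to a fuller document. It stands that the post-period source is inferred. But the article does fix the numerator, denominator, model and comparison, and it ties the duplicate rules for this analysis to registry records. Anyone following that wording would most naturally count registry records after activation and something else before it.

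A reader might infer that the bias always favours the intervention. The documents do not support that. Participation is voluntary, registry entry is an extra step separate from the formal pathway, and potential duplicates are merged, so post-period counts could fall short. Upward bias is the likelier direction because State of the Art and Operational Gaps describes incomplete documentation and no unified information system.

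A reader might also conclude that the baseline covers a single season. The 3 months are a project phase shared with recruitment, not a stated counting window. Season is a risk only if the counts are confined to that phase. Unequal length alone is handled by the professional-month denominator.

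Finally, the IRR is not the only reporting outcome. Timeliness, follow-up documentation and pathway activation are also listed, although none has a pre-post model.

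**Conclusion.** The point holds as a should-fix. On the natural reading, the two periods draw on different sources, and the expected IRR with no change in reporting is the ratio of capture fractions: 1.11 to 2.00 if baseline captures 90% to 50% of what the registry captures. That range rests wholly on assumed fractions, so it shows what the design permits and is not an estimate of the bias. The error rates also depend on an assumed reporting rate and pre-period length. Upward bias is likely, but the direction is not guaranteed.

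It would be too strong to say that this undermines the study. The outcome is secondary, the System Usability Scale analysis is untouched, and the Sample Size Calculation section disclaims definitive evidence of effectiveness. What fails is the reading of this IRR as impact on reporting.

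**What to change.** Compute the IRR from one numerator with the same source, case definition and duplicate rule in both periods. One candidate is aggregate counts of suspected maltreatment reports made by the participating professionals through existing institutional channels. State the pre-period. Where logs allow, let it cover the same calendar months as the post-period, and leave the training phase out of both. Report registry records per month as uptake only. Where no common source exists, as may be so in some community settings, present the before-and-after figures descriptively and do not interpret them as impact on reporting.

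With equal capture in both periods, the expected IRR under no change is 1.00. This still requires log completeness to be stable over time, which should be stated as an assumption.

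The cost is a retrospective extraction of aggregate counts and a protocol amendment, which needs ethics committee approval before it takes effect. Recruitment and data collection have begun, but analysis has not, so the change can still be made before results are seen. The downsides are that suspicions entered in the registry but not formally reported drop out of the IRR, and that log completeness may vary between settings.
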